### Data management and quality control

3.6

All records will be collected by trained and qualified investigators and screened by a qualified investigator. Once the CRF is complete, the original record will not be changed, even if any modifications are made. The completed CRFs will be reviewed by a clinical inspector. Data entry and management will be guided by medical statisticians. To ensure the accuracy of the data, 2 data managers will input and proofread the data independently. Once the created database has been audited and verified to be correct, the data will be locked by the principal investigator and statistical experts. The locked database or files will not be changed and will be submitted to the research team for statistical analysis. In addition, all data sets will be managed and monitored by Guangzhou Hipower Pharmaceutical R&D Co., Ltd. It will audit trials and data stores on a weekly basis.

### Statistical analysis

3.7

#### Clinical data analysis

3.7.1

Data analysis will be performed by professional statisticians and principal investigator using IBM SPSS Statistics (Version 24.0 position IBM Corp., Armonk, NY). Statistical analysis included actual number of subjects selected, cases of detachment and rejection, demographic and other baseline characteristics, patient compliance, efficacy, and safety analysis. Categorical variables will be described by frequency tables or percentages and continuous variables will be described by mean ± standard deviation. Categorical data will be analyzed by chi-square test or Fisher exact test to compare the differences between the two groups. Besides, quantitative data with normal distribution will be analyzed by T test. If the data does not conform to normal distribution or variance uniformity, Wilcoxon rank sum test or Wilcoxon signed test will be used for comparison between the two groups. A 2-sided *P* < .05 indicates statistical significance. For missing data, sensitivity analysis will be conducted and the optimal approach to the imputation of missing data will be proposed.

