### Study design and recruitment

2.2

This clinical study is a single-center, randomized, double-blind, double-simulation trial comparing TXACD with pinaverium bromide tablets (PBT) in patients with IBS-D, which will be performed lasting totally 10 weeks. At the initial run-in period (weeks −2–0), we will assess eligibility and seek in-formed consent. Then, coming to the treatment period (weeks 0–4), eligible subjects will be randomly assigned to one of two groups (TXACD group and PBT group) in a 1:1 ratio and get blinded treatment of 4 weeks. Finally, we will have a follow-up (week 8) 4 weeks after the treatment. This study involves 5 site visits (week −2, week 0, week 2, week 4, and week 8) and 6 call visits (weekly call during the treatment period and follow-up). At end of this trial, the primary outcome and the secondary outcome will be evaluated. We will obtain peripheral venous blood from partial IBS-D patients (n = 8 for TXACD group) before and after treatment and recruited healthy controls group (n = 4) for the assessment of mechanistic outcome. The process of the study and visit schedule is schematically shown in Figures 1 and 2.

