**Figure 2 F2:**
[figure not shown]
Recommended protocol items: visit schedule for enrollment, intervention, and assessments. AR = adequate relief, IBS = irritable bowel syndrome, IBS-QOL = IBS-quality of life questionnaire, IBS-SSS = IBS-symptom severity score, PBT = pinaverium bromide tablets, TCM = traditional Chinese Medicine, TXACD = Tong-Xie-An-Chang Decoction.

All 72 IBS-D patients participating in this study will be recruited from the gastroenterology department clinic or ward at Dongfang Hospital, Beijing University of Chinese Medicine. And we will additionally recruit 4 healthy controls.

According to the statistical minimum requirements for clinical efficacy evaluation of the two groups, the sample size of each group will be estimated to be 30 cases, with a total of 60 cases in both groups. After the shedding rate is calculated at 20%, the total number of cases in this study will be determined to be 72 cases.

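### Section 3.7.1 sends normally distributed data with unequal variances to the Wilcoxon rank sum test, which is not a remedy for unequal variance; the effect is modest and confined to continuous secondary outcomes

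*Protocol article*

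**What the plan says.** Section 3.7.1 (Clinical data analysis) sets one rule for all continuous outcomes.

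- Summary: "continuous variables will be described by mean ± standard deviation".
- Default comparison: "quantitative data with normal distribution will be analyzed by T test". No unequal-variance version is named.
- Fallback: "If the data does not conform to normal distribution or variance uniformity, Wilcoxon rank sum test", or the Wilcoxon signed test, for the comparison between the groups.
- Threshold: "A 2-sided *P* < .05 indicates statistical significance".

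The article does not say how normality or equality of variances will be judged, and it does not say what quantity the rank test is meant to compare.

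The primary outcome (Section 3.4.1) is a responder rate and adequate relief (3.4.4) is yes/no, so both fall under the chi-square or Fisher rule. The continuous rule reaches IBS-QOL (3.4.5) and the TCM syndrome score (3.4.3) where it is analysed as a score and not as an efficacy rate.

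**The concern.** The rank sum test takes its reference distribution from all allocations of the pooled ranks to the two groups. That is valid when the two distributions are the same, including their variances. A failed variance check says that they are not. The rule therefore moves the analyst to a test whose null hypothesis the trigger has just contradicted.

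The direct remedy for unequal variance in normal data is the unequal-variance (Welch) t test, which keeps the comparison on the means that the article plans to report. Under the rule as written, a secondary outcome would show two means and two SDs beside a P value that is not calibrated for the difference between those means, and that comes without an estimate of that difference. The stakes are a somewhat raised rejection rate when the means are equal and a small loss of power when they differ.

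**Working it through.** **Inputs from the article.** Allocation: "randomly assigned to one of two groups (TXACD group and PBT group) in a 1:1 ratio" (Section 2.2). Size: "the sample size of each group will be estimated to be 30 cases, with a total of 60 cases in both groups", then "After the shedding rate is calculated at 20%, the total number of cases in this study will be determined to be 72 cases" (same section). The level is two-sided 0.05 (3.7.1).

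**Arm sizes.** 60 × 1.2 = 72, which reproduces the stated total, so 72 / 2 = 36 per arm. If one arm loses 20%, 36 × 0.8 = 28.8, or about 29. The check therefore uses 36/36 and 36/29.

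**Assumed, because the article gives no figure.** SD ratios of 1 to 4, normal data, and a Levene test at 0.05 as the variance check.

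**Tests compared.** With arm means m1 and m2, SDs s1 and s2, and sizes n1 and n2:

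- Welch: t = (m1 − m2) / √(s1²/n1 + s2²/n2), with Satterthwaite degrees of freedom.
- Pooled t: the same numerator with one common variance.
- Wilcoxon rank sum: normal approximation to the rank statistic.

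**Rejection rate with equal true means, normal data** (40,000 simulated trials per row; the Monte Carlo standard error near 5% is √(0.05 × 0.95 / 40,000) = 0.0011):

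| Arms | SD ratio | Wilcoxon | Pooled t | Welch | Levene fires |
|---|---|---|---|---|---|
| 36/36 | 1 | 0.048 | 0.049 | 0.049 | 5% |
| 36/36 | 1.5 | 0.053 | 0.051 | 0.051 | 59% |
| 36/36 | 2 | 0.057 | 0.051 | 0.049 | 96% |
| 36/36 | 3 | 0.067 | 0.052 | 0.049 | 100% |
| 36/36 | 4 | 0.076 | 0.053 | 0.050 | 100% |
| 36/29, smaller arm more variable | 2 | 0.068 | 0.068 | 0.051 | 93% |
| 36/29, smaller arm more variable | 3 | 0.080 | 0.074 | 0.049 | 100% |
| 36/29, larger arm more variable | 3 | 0.056 | 0.034 | 0.050 | 100% |

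A separate run gave 5.6% and 6.6% for the Wilcoxon test at 36/36 with ratios 2 and 3, and 8.3% at 36/29 with ratio 3. These agree with the table within simulation error.

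**Reading the table.**

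- Once the SD ratio reaches 2 the variance check nearly always fires, so the rule is in effect the Wilcoxon test. Switching on the Levene result gave 0.057 at ratio 2 and 0.067 at ratio 3 with 36/36.
- At 36/36 the pooled t test already holds its level closely, so the switch repairs nothing.
- At 36/29 the pooled t test does go wrong when variances differ. The Wilcoxon test does not cure that; Welch does.

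**Power.** Take SDs of 1 and 2, 36 per arm and a mean difference of 1 (assumed). The standard error is √(1/36 + 4/36) = 0.373, so the difference is 1 / 0.373 = 2.7 standard errors. Simulated power is 72% for the Wilcoxon test and 75% for Welch.

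**The case against.** **No treatment effect means no inflation.** If treatment changes nobody's outcome, the two arms of a randomised trial share one distribution and the rank sum test holds its level (0.048 at SD ratio 1). The excess appears only when the treatments change the spread while the means tie, and rejection is then not a false claim that the distributions differ. This stands. It limits the point to reading the P value as evidence about means. The article states no mean-difference estimand; that reading is inferred from the mean ± SD summary.

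**A much larger figure is tempting.** With skewed scores (gamma, shape 2, SD ratio 2, equal means, 36 per arm) the whole rule rejects about 16%, and a reader might charge this to the variance condition. It does not belong there. In such data a normality check (Shapiro at 0.05) fires in 97% of trials, and rejection is about 16.5% with or without the variance condition. The figure comes through the separate normality condition, and the article gives no SDs or distribution shapes that would show these scores to be so skewed.

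**The rule is a common convention with a narrow reach.** Also true. Adequate relief is binary, and the TCM score is converted to an efficacy rate as well, so IBS-QOL may be the only outcome fully exposed. That bears on importance. It does not make unequal variance a reason to use the rank sum test.

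**Conclusion.** The point holds in a limited form and is a minor one. Unequal variance alone should not move normal data to the rank sum test when means are reported. With equal means the cost is about 0.6 to 1.6 percentage points above the nominal 5% at 36 per arm (SD ratios 2 to 3) and about 3 points at 36/29 with the smaller arm three times as variable, plus about 3 points of power at SD ratio 2. These sizes rest on normal data, assumed SD ratios and an assumed Levene check; the actual ratio is unknown.

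A reader might infer that the primary result is at risk. It is not, because the primary outcome is a binary responder rate. A reader might also conclude that the rank test should be demoted for all continuous data. That would override the normality condition as well. It is a trade-off that the evidence on the variance condition does not settle.

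**What to change.** In Section 3.7.1, delete unequal variance as a condition for the Wilcoxon test and state: *Normally distributed continuous outcomes will be compared with the unequal-variance (Welch) t test and reported as a mean difference with 95% CI, without a preliminary variance test. Where the Wilcoxon rank sum test is used for non-normal data, it will be reported as a test of a difference between distributions, described by P(X>Y), and not as a test of means.*

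This takes two sentences. SPSS, the named software, already prints the Welch result in its standard t-test output. The only statistical cost is a negligible loss of degrees of freedom when the variances are equal.

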### Intervention schedule

3.2

TXACD granule or placebo will be orally administered one packet after dissolved twice a day (1 h after the meal) for 4 weeks. Pinaverium bromide tablets or placebo will be administered one tablet three times a day (swallowed with meals). During the study, participants will be asked to stop taking the medications associated with IBS-D. Probiotics, functional foods and dietary supplements are also banned. Participants will be obligated to fill out daily study diaries, including medication administration records, accompanying treatments, and dietary questionnaires to help check compliance and statistically correct dietary bias. The presence of worsening IBS-D symptoms, which require recording in the Case Report Form (CRF), allows rescue medication to be used for less than 1 week.

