#### Primary outcome

3.4.1

The primary outcome of our trial is the response rate to the IBS Symptom Severity Score (IBS-SSS).^[20]^ Respondents were defined as having 50% or more reduction in IBS symptoms compared to baseline. IBS-SSS will be evaluated at baseline, week 2, week 4 and week 8.

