#### Irritable Bowel Syndrome-Quality of Life Questionnaire (IBS-QOL)

3.4.5

IBS-QOL which reflects a combination of physical and mental health across eight dimensions, will be assessed at baseline, week 2, week 4 and week 8.

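### A paired Wilcoxon test is named for comparing two independent arms, no baseline-adjusted analysis is named for the continuous scores, and the listed tests cannot carry the promised dietary correction

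*Protocol article*

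**What the plan says.** Section 3.7.1 (Clinical data analysis) gives the tests. For categorical outcomes: "Categorical data will be analyzed by chi-square test or Fisher exact test to compare the differences between the two groups". For continuous outcomes: "quantitative data with normal distribution will be analyzed by T test". If normality or equality of variance fails: "Wilcoxon rank sum test or Wilcoxon signed test will be used for comparison between the two groups". The significance rule is "A 2-sided *P* < .05 indicates statistical significance".

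Three other sections bear on this:

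- **Design (2.2):** "eligible subjects will be randomly assigned to one of two groups (TXACD group and PBT group) in a 1:1 ratio". No matching or pairing of patients is described.
- **Outcomes (3.4.1, 3.4.3, 3.4.5):** for the primary scale, "IBS-SSS will be evaluated at baseline, week 2, week 4 and week 8". The TCM syndrome score has the same visits, and IBS-QOL "will be assessed at baseline, week 2, week 4 and week 8".
- **Intervention schedule (3.2):** the daily diaries include "dietary questionnaires to help check compliance and statistically correct dietary bias".

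**The concern.** Three things in the analysis section do not fit the rest of the article.

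1. A signed test works on within-pair differences. Two separately randomised arms provide no pairs, so the test cannot compare them without an invented pairing. The word joining the two Wilcoxon tests also leaves the choice between them open.
2. Baseline values exist for every scored scale, yet none of the named tests has a baseline term, and the tested quantity (post-treatment value or change) is not stated. With 30 evaluable patients planned per arm, the precision given up could be worth having.
3. A statistical correction for diet is promised, but t, Wilcoxon, chi-square and Fisher tests take no covariate. Diet recorded while on treatment is measured after randomisation. If treatment eases symptoms and patients then eat differently, diet lies on the path from treatment to outcome, and adjusting for it could distort the treatment effect.

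**Working it through.** **Inputs.** From the article: 30 evaluable patients per arm (section 2.2, taken as stated), 1:1 allocation, two-sided 0.05. Assumed, because the article gives no values: correlation r between baseline and follow-up of 0.3, 0.5 or 0.7; equal SD at both times; 80% power for the detectable difference; a true difference of 0.6 SD for the power illustration. The plan states no figure on this point that could be reproduced.

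**1. Signed test on independent arms.** One data set was simulated with 30 normal values per arm and a true difference of 0.5 SD. Pairing the arms at random 5,000 times gave signed-rank p-values from 0.0007 to 0.24, with 66% below 0.05. The rank-sum p-value on the same data was 0.058 and does not depend on any pairing. With no true difference and a pairing fixed at random (4,000 runs), the signed-rank test rejected in 4.8% and the rank-sum test in 4.9%. So the false-positive rate is nominal if the pairing is fixed blindly. The fault is that the result is undefined until someone chooses a pairing. If dropout leaves arms of unequal size, no complete pairing exists.

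**2. Precision from baseline.** Taking the variance of a post-score comparison as 1:

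- change scores: 2(1 − r)
- ANCOVA: 1 − r²
- ANCOVA relative to change scores: (1 − r²) / [2(1 − r)] = (1 + r)/2

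The detectable difference for post scores is (1.960 + 0.842) × √(2/30) = 0.72 SD. The other methods multiply this by the square root of their variance.

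| | r = 0.3 | r = 0.5 | r = 0.7 |
|---|---|---|---|
| ANCOVA variance vs post scores | 0.91 | 0.75 | 0.51 |
| ANCOVA variance vs change scores | 0.65 | 0.75 | 0.85 |
| Detectable difference, post scores (SD) | 0.72 | 0.72 | 0.72 |
| Detectable difference, change scores (SD) | 0.86 | 0.72 | 0.56 |
| Detectable difference, ANCOVA (SD) | 0.69 | 0.63 | 0.52 |
| Power at 0.6 SD, post scores | 64% | 64% | 64% |
| Power at 0.6 SD, change scores | 50% | 64% | 85% |
| Power at 0.6 SD, ANCOVA | 68% | 77% | 90% |

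ANCOVA is the most precise of the three at each correlation, so the gain does not depend on which quantity the authors meant to test.

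**3. Diet.** No arithmetic applies. Section 3.2 commits to a statistical correction using data the participants record during the study. Section 3.7.1 lists four kinds of test, none of which accepts a covariate. The two sections cannot both be carried out as written.

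**The case against.** The strongest reply is that choosing between a t test and ANCOVA is commonly left to an analysis plan, that an unadjusted comparison is unbiased under randomisation, and that a t test on change scores would use baseline. A reader might infer that the trial tests raw scores and ignores baseline. The article does not support that: the tested quantity is not stated, the primary response is a reduction of at least 50% from baseline, and the TCM efficacy grades are percentage decreases from baseline. What stands is narrower. The section does name its tests for continuous data, and a baseline-adjusted analysis is more precise than either quantity those tests could be applied to.

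On the signed test, the authors probably meant within-group change, and the correct rank-sum test stands in the same sentence. But the sentence assigns both to the between-group comparison. A reader might also infer an inflated false-positive rate; the simulation does not show one.

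On diet, a reader might infer that the correction is impossible. That would require section 3.7.1 to be an exhaustive list, and a fuller plan could name a model. The mismatch between the two sections remains. The bias is a possibility, since no adjustment model is stated.

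One might also object to the switch to a rank-sum test when variances differ, which does not cure unequal spread. With equal arms of 30 this matters little: simulated false-positive rates (normal data, equal means, 20,000 runs) were 5.1%, 5.7% and 6.6% at SD ratios of 1.5, 2 and 3.

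**Conclusion.** The point holds in three limited parts. The signed test is wrong as written for two independent arms, because its result hangs on an arbitrary pairing. The continuous scores have no named baseline-adjusted analysis and no stated tested quantity. This is a loss of precision that leaves validity intact, and it concerns secondary or supportive outcomes; the primary outcome is a binary response rate. Under the assumed correlations the avoidable excess is 9% to 49% of the variance if post scores are tested, and 15% to 35% if change scores are tested. These sizes rest on correlations and equal SDs that the article does not give. The dietary promise and the list of tests need to be reconciled, and on-treatment diet is an unsafe covariate for the treatment comparison.

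**What to change.** In section 3.7.1:

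- Where a rank test is needed between groups, use only the rank-sum test. Limit the signed-rank test to describing change within a group.
- Analyse the continuous TCM syndrome score and IBS-QOL by ANCOVA at a named visit, or by a mixed model over weeks 2, 4 and 8, with the baseline score as covariate. Report adjusted differences with 95% confidence intervals. Treat IBS-SSS total score the same way, labelled as supportive.

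In section 3.2, remove the dietary correction from the primary comparison. Report diet descriptively, or adjust for it in a sensitivity analysis labelled as such. Restricting the correction to diet recorded before randomisation is not a safe substitute, because the article does not show that such data are collected.

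The cost is wording, plus one supportive analysis of a score already collected. No new data are needed. The changes should be made before unblinding.

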#### Mechanistic data analysis

3.7.2

The differential expression analysis about mRNA for all pairwise comparisons: IBS-D patients versus healthy controls, TXACD (pre-treatment) versus TXACD (post-treatment), will be performed by Cuffdiff. An adjusted *P* < .05 (Student *t* test accompanied with Benjamini-Hochberg FDR adjustment) will be used as the cut-off point for significantly differentially expressed genes. Prediction of target genes will be performed using Pearson correlation test.

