### Collection of biological specimens

2.7

The participants’ blood, stool and urine samples will be collected before and after intervention, and clearly marked in a uniform format. A designated investigator will isolate T lymphocytes single cells from the blood samples in the laboratory. Then, the isolated single cells were put into 3.5 μ l lysate and repeatedly blown with a pipette for several times, and then immediately stored at -80°C, finally transported to Shanghai OE Biotech Co., Ltd (Shanghai, China) for transcriptome sequencing.

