#### Mechanistic outcome

3.4.6

We will analyze the single-cell sequencing profiling of the T lymphocytes in peripheral blood from the TXACD granule group (n = 8) at baseline and week 4, and healthy subjects (n = 4) at baseline. In IBS-D, a complete set of transcriptional deviations enables us to search for potential molecular mechanisms and specific diagnostic biomarkers. At the same time, the therapeutic targets and pathways of TXACD in IBS-D were clarified. On the Illumina HiSeq 2000 platform, the preparation and deep sequencing of the transcriptome libraries will be performed by Shanghai OE Biotech Co., Ltd (Shanghai, China).

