## Discussion

4

Diarrhea-predominant irritable bowel syndrome (IBS-D) is a chronic intestinal disease,^[22]^ which seriously affects the study and life of the patients. However, little is known about the pathogenesis of IBS-D. Therefore, there is no specific drug in treating IBS-D. Clinicians are accustomed to using symptomatic treatment, but the effect remains erratic.

At present, more attention has been focused on Traditional Chinese Medicine (TCM) with its well-defined and established therapeutic system.^[23]^ TCM, with traditional Chinese syndrome differentiation as the core, has a stable effect in the treatment of IBS-D. Tong-Xie-An-Chang Decoction (TXACD), created by professor [name] from Dongfang Hospital, Beijing University of Chinese Medicine, has been shown to be effective in relieving abdominal pain in IBS-D patients in our previous randomized positive controlled clinical trial.^[15]^ Simultaneously, in IBS-D experimental rat model, TXACD was proved that it could reduce the fecal water content and abdominal withdrawal reflex (AWR) score, used to evaluate visceral sensitivity.^[24]^ These results of clinical and animal experiments suggested that TXACD might be a novel and promising strategy for the treatment of IBS-D. However, the potential therapeutic mechanism of TXACD in treating IBS-D still remains to be uncovered.

Although IBS-D is traditionally considered to be a functional bowel disease, many studies have shown that patients with IBS-D have low-grade inflammation and abnormal T cell activation on microscopic and molecular levels.^[25–27]^ Nevertheless, most of these studies are based on tissue, cell population level and expressed cytokines. It is not clear what the difference, cell heterogeneity, is at the single cell level. Single-cell RNA-sequencing technology may help elucidate this possibility of understanding cell heterogeneity. In the present study, Single-cell RNA-sequencing analysis is used to evaluate the transcriptome changes of T lymphocytes in peripheral blood of patients so as to explore the mechanism of T lymphocyte heterogeneity changes in the pathogenesis of IBS-D using differential gene analysis and cellular heterogeneity analysis and reveal the mechanism of TXACD in treating IBS-D at single cell level.

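### One Student t test rule is fixed for both gene-expression contrasts, with no pairing for the 8 pre/post patients and no allowance for cells nested in patients

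*Protocol article*

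**What the plan says.** Section 3.4.6 (Mechanistic outcome) sequences T lymphocytes "in peripheral blood from the TXACD granule group (n = 8) at baseline and week 4, and healthy subjects (n = 4) at baseline". Section 2.2 gives the same numbers. The before and after samples therefore come from the same 8 people, and the 4 healthy subjects are sampled once.

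Section 2.7 makes the data single-cell: "A designated investigator will isolate T lymphocytes single cells from the blood samples in the laboratory". The Discussion intends to study T-cell heterogeneity "using differential gene analysis and cellular heterogeneity analysis", which needs several cells from each person. The number of cells per person is not given.

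Section 3.7.2 then covers both contrasts in one sentence: "IBS-D patients versus healthy controls, TXACD (pre-treatment) versus TXACD (post-treatment), will be performed by Cuffdiff". A gene counts as differentially expressed if its adjusted P is below .05, from a Student t test "accompanied with Benjamini-Hochberg FDR adjustment". The section does not state the unit of analysis, pair the samples, include a patient term or aggregate cells by patient.

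**The concern.** The two contrasts have different structures. IBS-D against healthy is a comparison of independent groups, 8 people against 4. Pre against post is a comparison within 8 people. In both, the cells of one person share that person's biology and sample handling, so they are not independent replicates. A two-sample t test on cells counts them as if they were. A two-sample t test on patient values ignores the pairing in the pre/post contrast.

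The gene list is the mechanistic result. The abstract and Discussion intend to draw disease biomarkers and therapeutic targets of TXACD from it, and the Introduction includes mechanism in the stated aim. False entries would become false biomarkers, and lost power would hide real treatment effects.

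**Working it through.** The plan's own figure is a threshold (adjusted P below .05), so there is no derived number to reproduce. The check is whether the nominal 0.05 level holds under each possible unit of analysis.

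**Inputs from the protocol article:** 8 patients measured twice and 4 controls measured once (sections 2.2 and 3.4.6); single cells from each blood sample (2.7); Student t test with BH at .05 (3.7.2).

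**Assumptions, not in the article:** cells per person and visit, *m*; ICC of expression within a person; pre/post correlation of patient values, ρ. The healthy comparison is taken to use the 8 patients' baseline samples.

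**A. Cells as the unit, 8 v 4.** The variance of the group difference is understated by the design effect DE = 1 + (*m* − 1) × ICC. True size at nominal 0.05 is about 2 × [1 − Φ(1.96/√DE)].

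| *m* | ICC | DE | 1.96/√DE | Size, formula | Size, simulated |
|---|---|---|---|---|---|
| 10 | 0.01 | 1.09 | 1.877 | 0.06 | 0.06 |
| 50 | 0.02 | 1.98 | 1.393 | 0.16 | 0.16–0.17 |
| 50 | 0.05 | 3.45 | 1.055 | 0.29 | 0.29–0.30 |
| 100 | 0.10 | 10.9 | 0.594 | 0.55 | 0.55–0.56 |

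**B. Cells as the unit, pre/post.** Part of the patient effect cancels, so DE = 1 + [*m*(1 − ρ) − 1] × ICC. With ρ = 0.5:
- *m* = 10, ICC 0.01: DE = 1 + 4 × 0.01 = 1.04; size 0.055 (simulated 0.056).
- *m* = 50, ICC 0.05: DE = 1 + 24 × 0.05 = 2.20; size 0.186 (simulated 0.186).
- *m* = 200, ICC 0.05: DE = 1 + 99 × 0.05 = 5.95; size 0.42 (simulated 0.42).

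The inflation is smaller than in A but in the same direction whenever *m*(1 − ρ) exceeds 1.

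**C. What BH does with these P values.** In simulations of 20,000 genes with no true difference, cell-level testing at *m* = 50 and ICC 0.05 passed 3,044 genes for 8 v 4 and 762 for pre/post. At *m* = 10 and ICC 0.01 it passed none in either contrast. Patient-level tests (paired for pre/post) passed 0 to 2 genes in every setting. BH controls the false discovery rate only when the P values it receives are valid.

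**D. Patient as the unit, 8 v 4.** A Student t test on one value per person has simulated size 0.050.

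**E. Patient as the unit, pre/post, 8 pairs.** The true variance of the mean difference is (1 − ρ) times what the unpaired test assumes. For a 1-SD shift, the unpaired noncentrality is 1/√(2/8) = 2.00 (14 df, critical value 2.145). The paired noncentrality is √8/√(2(1 − ρ)), which is 2.83 at ρ = 0.5 and 3.65 at ρ = 0.7 (7 df, critical value 2.365).

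| ρ | Size, unpaired | Size, paired | Power, unpaired | Power, paired |
|---|---|---|---|---|
| 0 | 0.050 | 0.049 | 0.46 | 0.41 |
| 0.3 | 0.024 | 0.051 | 0.46 | 0.54 |
| 0.5 | 0.011 | 0.050 | 0.46 | 0.68 |
| 0.7 | 0.003 | 0.050 | 0.46 | 0.88 |

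These are single-gene figures at unadjusted 0.05, not power for the BH-adjusted list.

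**The case against.** The strongest reply is that the article never says the test is unpaired or that cells are the unit. The name Student t test does not exclude the paired form, and the unit of analysis and the aggregation step are details that a condensed article may leave to the full protocol or analysis plan. A paired t test on per-patient values would hold its level, and so would an 8 v 4 test on one value per person.

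This stands in part. A reader might infer that the rule fails under every reading, or that the gene list is bound to have wrong error rates. The article does not support that: with the patient as the unit, the 8 v 4 contrast is sound, and the pre/post contrast fails only if it is unpaired. A reader might also infer that an unpaired pre/post test discards most of the power. At correlations of 0.5 and 0.7 the relative loss is 1 − 0.46/0.68, about one third, and 1 − 0.46/0.88, about one half; at zero correlation there is no loss. Cell count and ICC are unknown, and at the mild end the cell-level error is close to nominal.

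What does not stand is that nothing has been fixed. Section 3.7.2 commits to a tool, a test, an adjustment and a cut-off, and puts the within-patient contrast beside the independent one under the same rule. Section 3.7.1, by contrast, names both a rank sum and a signed Wilcoxon test for the clinical data. The objection is to a stated method that does not fit the stated design, not to missing detail.

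**Conclusion.** The point holds in conditional form. The rule in section 3.7.2 matches neither the pairing nor the nesting of the data, and the consequence depends on the unit of analysis:

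- **Cells as the unit:** too many false positives. For 8 v 4, the size runs from about 0.06 to about 0.55 over 10 to 100 cells and ICC 0.01 to 0.10; pre/post is inflated less. BH does not correct it.
- **Patient as the unit, unpaired pre/post:** too conservative, with size 0.011 to 0.003 and power 0.46 against 0.68 to 0.88 at correlations of 0.5 to 0.7. This costs discoveries and does not create false ones.
- **Patient as the unit, 8 v 4:** no error-rate problem.

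The two errors run in opposite directions and cannot both affect one contrast. Cell counts, ICC and correlation are assumptions. The design facts and the named test are in the article.

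This should be fixed, but it does not threaten the trial's main result. A reader might extend it to the efficacy findings; the article gives no ground for that, because the primary, secondary and safety outcomes do not use this analysis. The claims at risk are those about biomarkers and therapeutic targets.

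**What to change.** Replace the Cuffdiff and Student t rule in section 3.7.2 with an analysis that makes the patient the unit:

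1. Aggregate cells per patient and visit, within T-cell cluster where cell numbers allow, or fit a mixed model with a patient random effect.
2. For pre against post, block on patient (8 pairs).
3. For IBS-D against healthy, compare 8 with 4 at patient level.
4. Apply BH to the P values from these analyses.

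The cost is revised wording and a different script on the same samples; no further sequencing is needed. The downside is probably a shorter gene list for the healthy-control comparison, which then rests openly on 8 and 4 people.
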